## 3. Data Collection and Management

Demographic data, including the age, height, weight, body mass index (BMI), prenatal maximum weight, physical activity during pre-pregnancy and pregnancy, and background data including the working position, smoking, alcohol consumption, urine leakage, asthma, constipation, family history of PFD, delivery history of pregnancy, weight gain during pregnancy, and fetal weight, would be collected at the enrollment visit of the study; while the following questionnaires would be filled by all participants at baseline and at all follow-up visits: (1)The International Physical Activity Questionnaire Score-Short Form (IPAQ-SF), which were recommended as a cost-effective method to assess physical activity by nine questions recording the activity of four levels of intensities in short forms: vigorous-intensity, moderate-intensity, walking, and sitting [31];(2)The Pelvic Floor Distress Inventory Questionnaire-20 (PFDI-20) and Pelvic Floor Impact Questionnaire-7 (PFIQ-7), which were designed to comprehensively evaluate to what extent the lower urinary tract, lower gastrointestinal tract, and pelvic organ prolapse symptoms affect the quality of life of women who suffer from PFD [32];(3)The Female Sexual Function Index (FSFI-6) [33], a common tool that has been validated for clinical use for evaluating female sexual function in six terms [34,35];(4)The Pittsburgh Sleep Quality Index (PSQI), which was developed in 1989 and accepted as the most common measure of sleep quality [36].

Baseline demographic data, IPAQ-SF, PFDI-20, PFIQ-7, FSFI-6, and PSQI were integrated into a WeChat mini program and can be filled by the Participants themselves by scanning a QR code on WeChat, a social App that is commonly used by the public in China. The body mass index (BMI) among the demographic data and all the scores or grades for all the questionnaires can be automatically come out by the configured formulas in the WeChat mini program. 

Following the questionnaires in each of the visits would be the physical examination including PFM strength evaluation by Modified Oxford Grading (MOS) [3], pelvic organ prolapse quantitation (POP-Q) stage [5], vaginal relaxtity, symptomatic SUI detection and grading, pelvic floor surface electromyography (sEMG) based on Glazer protocol [37], pelvic floor ultrasound examination, quantitative measurement of pelvic sagittal rotation degree by X-ray, and evaluation of the overall body composition and strength. 

Pelvic floor surface electromyography (sEMG) would be tested based on Glazer protocol. The participants would be taught to contract the pelvic floor muscle correctly and will have one practice before testing.

SUI is defined by SUI symptoms or a positive result of the cough stress test. Before the cough stress test, participants are suggested to keep fully bladder. Positive result of the test is defined as involuntarily urinary leakage when asked to cough in the lithotomy position.

Pelvic floor ultrasound indicators, which include LAM thickness, diameter of the levator hiatus, and levator hiatus area, were measured using the proprietary software 4D View via transperineal ultrasound(GE Kretz Medizintechnik), a reproducible and reliable measurement of vaginal support [38].

The quantitative measurement of pelvic sagittal rotation degree on Spine X-ray (Definium7000, General Electric Company, Boston, MD, USA) was analyzed which includes the pelvic tilt angle, the sacral slope angle, the difference of sacral slope and pelvic tilt, the ratio of the pelvic tilt angle to the sacral slope angle, the ratio of the pelvic tilt angle to the pelvic incidence angle and sacral-femoral distance.

The change of the overall body composition would be analyzed through body composition analyzers (Inbody 770), and overall strength which would be measured through hand grip strength test and trunk endurance test. Body composition analyzers would analyze data regarding waist hip ratio, basal metabolic rate, body fat rate, etc. Hand grip strength would be measured by JAMAR Plus+ grip gauge. The measurement accuracy is 0.1 kg. The participants should not have visible hand defects. The grip gauge should be adjusted before measurement. When the participants hold the grip gauge, the second knuckle of the index finger should be at 90 degrees. At the same time, mark the best position of each hand on the grip meter. Before measurement, the participants should remove wrist jewelry to avoid injury. The left and right hand are measured alternately three times. Trunk endurance would be tested using the Plank test, Side bend test, and Biering–Sorensen Test [39]. All the participants were encouraged to keep the positions as long as possible. Time as recorded in seconds with a maximal length of 90 s.

## 4. Outcomes of the Study

The primary outcome will be the comparison of participants’ pelvic floor muscle strengths using MOS scale at the enrollment baseline and post intervention. The secondary outcomes will be: (1) the occurrence of SUI, (2) the change of the Pelvic floor ultrasound indicators, (3) change of the Pelvic Organ Prolapse Quantitation measured by callipers, (4) change of the pelvic sagittal rotation degree, and (5) the change of the overall body composition and strength. The list of data collection instruments and time of data collection is presented in Table 2 and Table 3.

The other secondary outcome measures involved in the Table 2 will be calculated and discussed separately.

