Pregnancy and vaginal delivery have independently been proved to be the risk factors for the development of severe urinary incontinent (SUI) as they could obviously weaken the pelvic floor muscle (PFM) strength. However, it was hard to evaluate patients’ muscle strength objectively; therefore, it was hard to validate whether a measure could be effective to have the weakened pelvic floor muscles be recovered before Modified Oxford scale (MOS) for muscle strength was published [3]. MOS provides quantitative scales for muscle strength, and it is simple and easy to apply clinically. It is becoming widely accepted method for pelvic floor muscle strength assessment since it was published. Literately and clinically, MOS 4 and 5 is identified as having “good” or “strong” muscle contraction which represents a normal condition of the pelvic floor muscles; relevantly MOS ≤3 indicates a weak contraction or no contraction being felt [4]. Some studies suggested that pelvic floor muscle strength be correlated with the incidence of pelvic organ prolapse (POP). Thus, Pelvic Organ Prolapse Quantification (POP-Q) was developed for evaluation of the pelvic floor muscle [5]. Borello-France et al. [6] used POP-Q to evaluated women’s pelvic floor muscle in their studies and argued that women with stage II of prolapse were better than those with stage III or IV in elevating their pelvic floor, and also would be easier to get benefit from PFM training than those over stage III. Scientific evidence showed that 10–20% of patients who were not intervened for the clinically confirmed POP got progressed in term of POP-Q scoring in 2-year follow-up [7,8], so early prevention or treatment should have high priority. The incidence rate of POP is higher in middle aged and elderly women. PFM training is recommended to women postpartum for it reduces the incidence of PFD during 6–12 months postpartum [9] and should possibly reducing the incidence of diseases from muscle dysfunction related to the anatomical changes with aging [10]. A program of supervised PFM training was recommended as a first option for women with symptomatic POP-Q stage I or stage II [11]. MOS and POP-Q can be the objective indicators be used to validate the effectiveness of any measure in improving PFM.

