### 2.3. Exclusion Criteria

Participants will be excluded if they are: (1) confirmed by postpartum pelvic examination to be >grade 3 of pelvic floor muscle strength by Modified Oxford Scale (MOS); (2) ≥stage III for Pelvic Organ Prolapse Quantification (POP-Q); (3) symptomatically confirmed to have severe urinary incontinence (Women with more than one incontinent episode per day AND an important volume of urine loss [28] or urine leakage occurred in a quiet state were classified as having severe urinary incontinence); or (4) any limb dysfunction that unenabled women to take this training. A participant will be recorded as“ drop off from trial” if she becomes pregnant during the follow-ups.

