### 4.2. Statistical Analysis

Data will be analyzed using SPSS version 26.0 (SPSS, Inc., Chicago, IL, USA) and the statistically significant difference will be identified if *p* < 0.05. Descriptive statistics including numbers and proportions, means and standard deviations, or medians (P25, P75) will be used. Group differences in the primary and secondary outcomes will mainly use chi-square and student’s t tests. For primary outcome, we will count the rate of pelvic muscle strength reaching grade 4 at 6 months postpartum between EG and CG by chi-square test or Fisher’s exact test as appropriate. Analysis of the primary and secondary outcomes will be based on an intention-to-treat basis in consideration of the drop-offs from the follow-ups and be conducted by the statistician at Peking University Clinical Research Institute. For comparison between groups of quantitative data, the analysis of variance or Wilcoxon rank sum test will be used according to the data distribution; chi square test or exact probability method is used for counting data (if chi square test is not applicable), Wilcoxon rank sum test or CMH test is used for grade data, and logistic regression analysis is used for correlation analysis. Repeated ANOVA will be used to assess within-patient correlation. and multivariable linear regression models if potential confounders were imbalanced.

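### The SUI secondary outcome names no visit and makes no use of baseline SUI, so it loses precision and cannot separate new onset from persistence or remission

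*Protocol article*

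**What the plan says.** - **Outcome.** Protocol article, section 4: "The secondary outcomes will be: (1) the occurrence of SUI". No visit is attached, although section 2.6 schedules two assessments after baseline (18 to 24 weeks and one year postpartum). The other four outcomes in that list are worded as changes; this one is not.
- **Case definition.** Section 3: "SUI is defined by SUI symptoms or a positive result of the cough stress test". This is a status at a visit and does not refer to status at entry.
- **Eligibility.** Section 2.3 excludes women "symptomatically confirmed to have severe urinary incontinence", with severity defined by frequency and volume or by leakage at rest. Milder leakage does not exclude.
- **Baseline data.** Section 3 includes "symptomatic SUI detection and grading" in the examination at each visit and records "urine leakage, asthma, constipation, family history of PFD" at enrollment. Table 2 shows the cough stress test at all three visits in both arms.
- **Analysis.** Section 4.2: "Analysis of the primary and secondary outcomes will be based on an intention-to-treat basis", and "Group differences in the primary and secondary outcomes will mainly use chi-square and student’s t tests". The section mentions a CMH test for graded data, logistic regression for correlation analysis, and multivariable linear models where confounders are imbalanced. It does not tie any of these to a binary SUI outcome with baseline SUI as a stratum or covariate.
- **Abbreviation.** The Introduction spells the term out differently: "the development of severe urinary incontinent (SUI".

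**The concern.** Women who leak at entry and women who do not are both in the comparison. A woman with SUI at entry who still has it at follow-up counts as a case. A woman whose SUI has resolved counts the same as one who never leaked. The word occurrence suggests new cases, but the eligibility rule and the definition do not deliver a count of new cases.

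There are two costs. First, baseline SUI is probably among the better predictors of later SUI, and the stated test leaves it out. That gives up precision and lets chance imbalance at baseline pass into the estimate. Second, the pooled proportion cannot tell the reader whether training stopped new SUI or helped existing SUI resolve. These are different clinical messages, and the Introduction speaks of both prevention and treatment. Without a named visit, the result could also come from either of two time points.

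**Working it through.** **The plan's own figure.** The article states no rate or power for SUI. Its only calculation is for the MOS outcome: Φ(0.2/√(0.2·0.8/106 + 0.6·0.4/106) − 1.96) = Φ(3.256 − 1.96) = 0.9025, which matches the stated 90.248% at one-sided alpha 0.025. It has no bearing on this point, except that 106 evaluable women per arm is used below.

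**Step 1: who is in the comparison.** Section 2.3 removes severe incontinence only, section 3 defines SUI by symptoms or a cough test, and section 4.2 applies intention to treat. Nothing restricts the outcome to women free of SUI at entry. The pooling therefore follows from reading these sections together; no sentence states it.

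**Step 2: can the pooled proportion separate the two effects?** Let b be SUI prevalence at entry, p the persistence among those women and i the new onset among the rest. Prevalence at follow-up is b·p + (1 − b)·i.

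Assumed for the control arm: p = 60%, i = 10%. None of these rates comes from the trial. The 30.9% row uses the Introduction's prevalence of any urinary incontinence in Chinese women, as one point in the range only.

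| b | Control | Training arm, onset halved to 5%, p unchanged | Persistence giving the same result, i unchanged |
|---|---|---|---|
| 10% | 15.0% | 10.5% | 15% |
| 20% | 20.0% | 16.0% | 40% |
| 30.9% | 25.5% | 22.0% | 48.8% |
| 40% | 30.0% | 27.0% | 52.5% |

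For b = 20%: control is 0.2·0.6 + 0.8·0.1 = 0.20. Prevention only is 0.2·0.6 + 0.8·0.05 = 0.16. Remission only is 0.2·0.4 + 0.8·0.1 = 0.16. The two routes give the same pooled result in every row.

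**Step 3: what ignoring baseline costs.** The share of outcome variance that lies between the baseline strata is b(1 − b)(p − i)² / [P(1 − P)], where P is prevalence at follow-up. For b = 20%, p = 60%, i = 10%: 0.16·0.25 / 0.16 = 25%. Over b = 10% to 40% the share is:

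- p = 60%: 17.6% to 28.6%
- p = 40%: 7.2% to 12.6%

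On the risk-difference scale, a stratified analysis removes roughly this share of the variance.

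**Step 4: chance imbalance.** With 130 women randomized per arm, the standard error of the difference in baseline prevalence is √(2b(1 − b)/130), which is 5.0 points at b = 20% and 6.1 points at b = 40%. Multiplied by p − i = 0.5, about 2.5 and 3.0 points pass into the unadjusted difference at follow-up. The prevention-only differences in step 2 are 4.0 and 3.0 points at those values of b.

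**Step 5: how large are the subgroups?** With 106 evaluable per arm:

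| b | Without SUI at entry, per arm | With SUI at entry, per arm |
|---|---|---|
| 10% | 95 | 11 |
| 20% | 85 | 21 |
| 30.9% | 73 | 33 |
| 40% | 64 | 42 |

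At b = 20%, new onset of 10% against 5% means 106·0.8·0.10 = 8.5 against 106·0.8·0.05 = 4.2 expected events. That supports description but not a firm test.

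**The case against.** The strongest reply is that randomization and intention to treat make the comparison of SUI at follow-up in all women a valid estimate of the total effect. The second hypothesis in the Introduction concerns overall function, including pelvic floor function, and fewer women with SUI by either route answers it. All of this stands: the defect is not a bias.

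A reader might infer that the plan would present fewer cases of SUI as prevention of new cases, or that a prevention claim must rest on the new-onset comparison alone. The documents do not support that. No section commits to a prevention claim for this outcome, the pooling is inferred, and step 5 shows that the new-onset subgroup could not carry such a rule.

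It may also be said that baseline data, grading and an imbalance provision already exist. They do, but the outcome as worded does not use the baseline status or the grade. The imbalance provision names a linear model, which suits a binary outcome poorly, and it applies only if imbalance is found.

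Finally, if SUI meant severe urinary incontinence, as the Introduction's expansion has it, the exclusion rule would remove every case at entry and occurrence would be incidence. The cough-test definition and the grading of SUI in section 3 contradict that reading. The conflict is real and needs resolving, but it does not remove the point.

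An analysis plan that is not shown may add detail. The point rests on what the article itself fixes: the outcome wording and the named test.

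**Conclusion.** The point holds as one of definition and efficiency in a secondary outcome. As written, the outcome is best read as SUI prevalence at an unnamed follow-up visit, compared without using baseline SUI. The comparison is valid, but it is less precise than it could be, and it cannot distinguish new onset from persistence or remission.

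The documents give no baseline SUI rate for this trial and no persistence or onset rates, so the sizes are illustrations. Over the assumed ranges, baseline SUI accounts for about 7% to 29% of the outcome variance, with the lower end applying if SUI at entry mostly resolves in both arms. That the two routes cannot be told apart does not depend on any particular rate, as long as some women have SUI at entry.

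**What to change.** 1. Define the outcome as SUI status (symptoms or positive cough stress test) at the second assessment, 18 to 24 weeks postpartum, and at one year, in all randomized women.
2. Compare the arms by logistic regression adjusted for baseline SUI, or by a CMH test stratified by baseline SUI, in place of the unadjusted chi-square test.
3. Report descriptively, by arm, new-onset SUI among women without SUI at entry and remission among women with SUI at entry, noting that these groups are small.
4. Describe the overall result as prevalence of SUI and not as incidence.
5. Reconcile the Introduction's expansion of SUI with the definition in section 3.

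The cost is outcome wording, one change of test and two descriptive table rows. All the data are already scheduled. The subgroup rows will have wide intervals, and a logistic model gives an odds ratio conditional on baseline SUI, so the prevalence in each arm should be shown beside it.

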**Cooling Down**	Dynamic stretching, including upper and lower limbs, waist, back, and abdomen stretching and pelvic floor muscle relaxation with mini foam axis.			

**Table 2 ijerph-19-11073-t002:** Data collection and follow-up instruments.

		EG	CG	EG	CG	EG	CG
Baseline screen, Informed consent, Randomization							
The follow-up visits		The First		The Second		The Third	
Demographic data collection		◯	◯				
The MOS		●	●	●	●	●	●
POP-Q stage		●	●	●	●	●	●
Cough stress test		●	●	●	●	●	●
Vaginal relaxity		●	●	●	●	●	●
Pelvic floor electrophysiological test		◎	◎	◎	◎	◎	◎
Pelvic floor ultrasound		◎	◎	◎	◎	◎	◎
Spine X-ray		◎	◎	◎	◎	◎	◎
Body Composition		◎	◎	◎	◎	◎	◎
Hand grip test		◎	◎	◎	◎	◎	◎
Trunk endurance test		◎	◎	◎	◎	◎	◎
Questionnaires	PFDI-20	◯	◯	◯	◯	◯	◯
	PFIQ-7	◯	◯	◯	◯	◯	◯
	FSFI-6	◯	◯	◯	◯	◯	◯
	IPAQ-SF	◯	◯	◯	◯	◯	◯
	PSQI	◯	◯	◯	◯	◯	◯
Training record				✷	✷(if any)		
RPE				✷			
Adverse Event				☐	☐		

●: Data would be collected by pelvic floor professionals via vaginal palpation. ◎: Data would be collected by experienced General specialists as the examiners. ◯: data would be collected by requesting all participants to give answers through scanning a QR code. ✷: Recording by all the participants in EG only per their training record and RPE score given by themselves.: Optional items. Abbreviations: MOS: The modified Oxford Scale [3], which needs to be performed by inserting two fingers into the vagina for approximately 4 cm to feel the FPM contraction and give scale ranging from 0 (no contraction) to 5 (strong contraction).; POP-Q [5]: pelvic organ prolapse quantitation; PFDI-20: The Pelvic Floor Distress Inventory Questionnaire-20; PFIQ-7: Pelvic Floor Impact Questionnaire-7; FSFI-6: The 6-item Female Sexual Function Index; IPAQ-SF; International Physical Activity Questionnaire Score-Short Form; RPE: Ratings of Perceived Exertion.

**Table 3 ijerph-19-11073-t003:** Outline of Soring for general pelvic floor function.

Testing Items	Indicators	Compute Value	Score Value
POP-Q	Stage 0	0	
	Stage I	1	
	Stage II	2	
	Stage III	3	
	Stage IV	4	
Cough stress test	Yes	1	
	No	0	
Vaginal relaxation	≥4 fingers	4	
	>3 fingers, and <4 fingers	3	
	=3 fingers	2	
	>2 fingers, and <3 fingers	1	
	≤2 fingers	0	
Pelvic floor electrophysiological test [40]	<20 cm^2^Hg	1	
	≥20 cm^2^Hg	0	
			* Total Score ^1^
PFDI-20	-	Comprehensive score	
PFIQ-7	-	Comprehensive score	
FSFI-6	-	Comprehensive score	
			* Total Score ^2^

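### The POP-Q secondary outcome is defined as a calliper measurement, but the data-collection text and tables schedule only an ordinal stage under a palpation legend

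*Protocol article*

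**What the plan says.** Section 4 (Outcomes of the Study) gives secondary outcome 3 as "change of the Pelvic Organ Prolapse Quantitation measured by callipers". It names no POP-Q point and no summary. The same paragraph then states: "The list of data collection instruments and time of data collection is presented in Table 2 and Table 3".

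The places that say what is collected read as follows:

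- **Section 3 (Data Collection and Management)** lists, among the examinations at each visit, "pelvic organ prolapse quantitation (POP-Q) stage".
- **Table 2** has one POP-Q row, headed as stage and marked with the filled circle for both arms at all three visits. The legend for that symbol reads: "Data would be collected by pelvic floor professionals via vaginal palpation".
- **Table 3**, titled "Outline of Soring for general pelvic floor function", codes POP-Q stages 0 to IV as 0 to 4.
- **Section 2.3 (Exclusion Criteria)** removes women at stage III or higher, so stage at entry is 0, I or II.
- **Section 4.2 (Statistical Analysis)** provides tests for quantitative data (analysis of variance or Wilcoxon) and, separately, says "Wilcoxon rank sum test or CMH test is used for grade data". It does not say which applies to POP-Q.

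**The concern.** Callipers yield a length, and a stage is a category. A change in length cannot be recovered from a recorded stage, so the definition in Section 4 and the items scheduled elsewhere describe two different variables with two different instruments. This is not detail that a condensed article leaves out: the article states both versions.

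Two things follow. First, the outcome variable is not fixed. Section 4.2 has a test ready for either scale, so the choice could be made after the data are seen. Second, if stage is what is analysed, the entry restriction limits its use in the direction the trial hopes to show: a woman at stage 0 cannot improve, a woman at stage I can improve by one step, and a woman at stage II by two. Section 1 names POP-Q beside MOS as an objective indicator for validating effectiveness, so the outcome is not incidental.

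**Working it through.** **Design figure.** The article gives no effect size, SD, stage distribution or power for POP-Q. Its one design calculation concerns the improvement rate in MOS: 106 per group and 90.248% power, for proportions of 0.2 and 0.6 against a null difference of 0.2. With a one-sided alpha of 0.025 (not stated, but it reproduces the figure):

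Power = Φ(0.2 / √((0.2×0.8 + 0.6×0.4)/106) − 1.96) = Φ(3.256 − 1.960) = Φ(1.296) = 0.902

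The figure reproduces and has no POP-Q input, so nothing below touches it.

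**The text set side by side.**

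| Place | Variable | Instrument | Scale |
|---|---|---|---|
| Section 4, outcome 3 | change in POP-Q | callipers | implied length |
| Section 3 | POP-Q stage | not stated | ordinal |
| Table 2 and legend | POP-Q stage | vaginal palpation | ordinal |
| Table 3 | stage 0 to IV, coded 0 to 4 | not stated | ordinal |
| Section 2.4 | POP-Q, unqualified | not stated | not stated |

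Section 3 goes on to describe the electromyography, cough test, ultrasound, X-ray, body composition, grip and endurance measurements, but says nothing more about POP-Q. The conflict is therefore not settled anywhere in the article.

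**What analysing stage alone would cost.** This is an illustration on assumptions, not a result from the document. Suppose a normally distributed measure underlies the stage and is grouped into three categories with proportions p₁, p₂, p₃. Let φ₁ and φ₂ be the standard normal densities at the two cut-points. The share of Fisher information on a small location shift that survives grouping is

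φ₁²/p₁ + (φ₁ − φ₂)²/p₂ + φ₂²/p₃

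- Equal thirds: cut-points ±0.431, φ = 0.364, giving 2 × 0.364² / 0.333 = 0.79.
- 20/50/30%: φ₁ = 0.280, φ₂ = 0.348, giving 0.392 + 0.009 + 0.403 = 0.80.
- 10/60/30%: 0.76.
- 50/40/10%: φ₁ = 0.399, φ₂ = 0.175, giving 0.318 + 0.125 + 0.308 = 0.75.
- 5/85/10%: 0.53.
- 5/15/80%: 0.52.
- 2/96/2%: 0.23.

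For scale, against the 2 × 106 = 212 women in the sample-size calculation, retention of 0.75 to 0.80 corresponds to about 159 to 170 women with the ungrouped measure (0.75 × 212 = 159; 0.80 × 212 = 170). Retention of 0.52 corresponds to about 110.

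**A second figure, and why it is not the loss.** Assume a leading point with mean −2 cm and SD 1 cm, stage cut-offs at −3, −1 and +1 cm, and a 0.5 cm improvement in every woman. The share who change stage is

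[Φ(−0.5) − Φ(−1)] + [Φ(1.5) − Φ(1)] + [Φ(3.5) − Φ(3)] = 0.150 + 0.092 + 0.001 = 0.24

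Means from −2.5 to −1 cm give 0.24 to 0.25. The denominator includes women already at stage 0 (Φ(−1) = 16% at mean −2 cm, 31% at −2.5 cm), who have no lower stage to reach. The share of individuals who change category is also not the information lost in a comparison of two arms.

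**The case against.** The strongest reply is that this is a mismatch of wording. Section 4 supplies an instrument, and Section 2.4 lists POP-Q among the gynaecologists' examinations without restricting it to stage. A schedule row names an examination, not the fields of the case-report form, which a condensed article leaves to the full protocol. The palpation symbol also covers the cough stress test, which Section 3 defines by observed leakage, so the legend is loose and does not show that callipers are unused. Table 3 feeds a composite score and does not define outcome 3. Section 4.2 has tests for both scales.

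Much of this stands, and it rules out two stronger readings.

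- A reader might infer that the calliper outcome cannot be derived at all. The document does not support that. If the points are assessed in order to assign a stage, the measurements arise at the same examination, and only their recording is left unstated.
- A reader might infer that most real change would be missed and that a null POP-Q result would be uninformative. No distribution, cut-off or expected shift in the document supports that. The 24% to 25% above rests wholly on assumed values and does not measure lost information.

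The floor is also one-sided. The stage limit applies at entry only, Table 3 keeps codes for stages III and IV, and Section 1 motivates the trial partly by progression without intervention, so worsening can be recorded.

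The reply does not remove the conflict. Section 4 itself names the two tables as the list of instruments, and they give a different variable from the one it defines. Having a test for either scale leaves the choice open.

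**Conclusion.** The point holds as an internal contradiction: Section 4 disagrees with Section 3 and Tables 2 and 3 on the instrument and scale of secondary outcome 3, and no measured POP-Q value is listed for collection.

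If stage alone is analysed, improvement has a floor and some precision is lost. On the assumption of an underlying normal measure, the loss is roughly 20% to 25% of the information when women are spread over three stages. It rises to about half or more when 80% or more of women share one stage. The actual size cannot be given, because the stage distribution is not stated.

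The matter concerns one secondary outcome and should be corrected. The primary outcome and the sample size are unaffected.

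**What to change.** 1. Reconcile Section 3, Section 4, and Tables 2 and 3 so that they name the same POP-Q variable and instrument. Correct the Table 2 row and legend to match.
2. Record the individual POP-Q point measurements in cm at all three visits.
3. Name one measured value, for example the leading point, at the second visit (18th to 24th week postpartum), adjusted for its baseline value, as the POP-Q secondary outcome. State the matching analysis in Section 4.2.
4. Derive stage from the same measurements and report it descriptively, including any worsening to stage III or IV.

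The cost is a few case-report-form fields, one table edit and a sentence in Section 4.2. On the assumption that the points are assessed anyway to assign the stage, no extra procedure is needed.
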